### Primary outcome measures

The primary outcomes for the study were changes in ADHD symptoms from baseline to week 6 (or from week 6-12) as measured by the K-ADHD-RS [38]. The K-ADHD-RS is an 18-item standardized, valid, reliable instrument for the diagnosis and also a weekly assessment tool for checking the of treatment response among children and adolescents with ADHD [39]. Each item on the instrument describes one of the symptoms of ADHD rated on a 0-3 point Likert scale (0 = never or rarely, 1 = sometimes, 2 = often, and 3 = very often) [39]. The principal investigator administered the K-ADHD-RS to the parent at each study visit. Nationally representative norms are available for the scale and were used to determine eligibility [39].

### Secondary outcomes

The Clinical Global Impression (CGI) rating scale is also a commonly used measure of symptom severity, treatment response, and the efficacy of treatments in treatment studies of patients with mental disorders [40]. The Clinical Global Impression severity scale (CGI-S) was used at week 3 and 6 (or weeks 3, 6, 9, and 12). CGI-S requires the clinician to rate the severity of the patient's illness at the time of assessment, relative to the clinician's past experience with patients who have the same diagnosis. Considering total clinical experience, a patient is assessed on the severity of mental illness at the time of rating on a 1-7 scale (1 = normal or not at all ill, 2 = borderline mentally ill, 3 = mildly ill, 4 = moderately ill, 5 = markedly ill, 6 = severely ill, and 7 = extremely ill) [41]. The Clinical Global Impression improvement scale (CGI-I) is used at week 3 and 6 (or weeks 3, 6, 9, and 12) to rate the worsening, maintenance, or improvement in global impairment of participants enrolled in the study compared with baseline [41]. The CGI improvement scale includes an eight-point scale for scoring (0 = not assessed, 1 = very much improved, 2 = much improved, 3 = minimally improved, 4 = no change, 5 = minimally worse, 6 = much worse, and 7 = very much worse) [41].

The Korean version of Child Behavior Checklist (K-CBCL) was used at week 3 and 6 (or weeks 3, 6, 9, and 12). CBCL has been proposed as a non-ideological measure to characterize comorbidity in individuals with ADHD [42,43]. The CBCL is an empirically derived, highly valid and reliable parent checklist of pediatric psychopathology that is composed of several dimensions and scored according to established algorithms [44]. As a parent-completed measure, the CBCL provides a common metric across patients and studies that is free from clinician interpretation [45]. Subsequent reports have proven the utility of this approach [46-50].

The Frankfurt Attention Inventory (FAIR) [51] measuring concentration behavior consists of 640 stimuli with high similarity that have to be discriminated against each other within 6 min. The FAIR test quantifies aspects of concentration behavior displayed in four test scores: marker value (MV) expresses comprehension of test instructions, performance value (PV) informs on the amount of attentively processed test items during a defined test period, quality value (QV) depicts the amount of attentively made decisions respective to the total amount of decisions, and the continuity value (CV) reflects the extent of continuously upheld concentration over the entire test duration. The FAIR task provides good test-retest reliability expressed as a Crohnbachs' alpha between 0.85 and 0.91 [51].

The Computerized Neurocognitive function Test (CNT) is used at week 3 and 6 (or week 3, 6, and 12). CNT is extremely sensitive to virtually all of the clinical conditions associated with cognitive dysfunction. It is capable of calculating reaction times with millisecond accuracy, and can generate massive amounts of precise data. In this study, CNT40^© ^(Maxmedica; http://www.maxmedica.co.kr, Seoul, Korea)[52] is selected to make cognitive evaluations of attention and memory function. CNT40 consists of 18-items: Digit Span Test, Visual Span Test, Auditory CPT, Auditory Controlled CPT, Visual CPT, Visual Controlled CPT, Crossover Test, Modality Shift Test, Word-Color Test, Trial Making Test, Card Sorting Test, Verbal Learning Test, Visual Learning Test, Hypothesis Formation Test, Finger Tapping Test, Raven's CPM, Raven's SPM and Color Trail Making Test. Among these items, the Digit Span Test, Visual Span Test, Auditory CPT, Visual CPT and Verbal Learning Test are used to assess attention and memory dysfunction in ADHD patients.

Korean version of Conners' parent Rating scale: short version (K-CPRS) [53,54] and Korean version of IOWA-Conners Rating scale: short version (K-IOWA) [55], which use observer ratings, are included to help assess ADHD and evaluate problem behavior in children and adolescents.

### Randomization and treatment allocation

This study is designed as a waitlist controlled open trial. Eligible participants were randomly allocated to one of two groups: group A (acupuncture) and group W (waitlist). In each group, participants were stratified according to the pharmacologic intervention at the initiation of the study. A computer generated randomization scheme was used. The principal investigator generated the random allocation sequences without any notice to sub-investigators. Stratified randomization was performed as a separate randomization procedure within each of two subsets of participants (without pharmacologic intervention, 1-60; with pharmacologic intervention, D1-D40. Other treatments were not concerned.) by using block size "4". Each number and its randomised letter (A or W) were placed in an opaque envelope. Each envelope was numbered consecutively from 1-60 and D1-D40. As each parent called to have their child screened, they were allocated the next consecutive number once they were eligible, so that for each eligible participant, no. 1 was allocated to envelope no. 1, etc. The screener was unaware of the sequence of group allocation at the time of screening phase. Hence, allocation was concealed at the time of recruiting.

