### Participants

Parents were initially screened by phone, and their children were included in the study if the inclusion criteria were met. The inclusion criteria includes being between 7-18 years of age, having a diagnosis of ADHD (any subtype) according to Diagnostic and Statistical Manual of Mental Disorders (DSM-IV) criteria and having an informed verbal and written consent from parents and participants. It did not matter whichever intervention (pharmacological, psychosocial therapy, educational, or occupational therapy, as examples) was used, if there were not any change of ADHD treatments/symptoms for the past 2 weeks. Exclusion criteria are a diagnosis of a developmental disorder, past history of epilepsy, the presence of another neurotic disorder, pregnancy, and any changes in medications during the course of the study. During waitlist period, a CGI-I score ≥6, is a cue for the participant to stop waiting and to drop-out.

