### Measures

DSM-IV ADHD diagnostic criteria [1,37] were used by the principal investigator to establish a diagnosis. Once randomised, participants were evaluated by the principal investigator during study visits at baseline and weeks 3 and 6 (or 3, 6, 9, and 12). The reliable and validated Korean version of the ADHD rating scale (K-ADHD-RS) [38] was used pre- and post-intervention as a primary outcome measure.

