One limitation of this study involves the waitlist for the controlled group. Many researchers commonly prefer placebo controlled designs to the waitlist ones in randomised control trials. Placebo effects of acupuncture were actively studied in many articles and sham acupuncture is a representative method for an acupuncture placebo tool. But there is a lack of consensus on the most valid approach to establishing an acupuncture placebo. So, important aspects of the placebo acupuncture control need to be considered. "Inert" is the main topic in placebo acupuncture control. Placebo acupuncture strategies mainly consist of superficial (or minimal) insertion, non-acupuncture insertion points insertion, and sham acupuncture. But each approach has some defects. First, a superficial (or minimal) insertion is not a real placebo method because it induces peripheral sensory stimulation. It does not seem possible to insert acupuncture needles without any sensory stimulation [64,65]. In fact, even a very mild form of placebo acupuncture seems to exert an effect [66]. Second, non-acupuncture insertion points may not be inert. Needling in the areas around the traditional acupuncture points may be equally efficient [66]. Acupuncture areas or zones are understood to be like acupuncture points in the current ongoing discussion. Third, some articles have suggested that sham acupuncture may not be inert [67,68]. Re-examination of acupuncture trials is needed, to ascertain whether a sham that was assumed to be inert was in fact not inert [67]. In this context, a placebo acupuncture, as a control intervention, is not adequate enough to observe acupuncture effects. Although waitlist is an imperfect control method as well, we used it to observe definite acupuncture effects in ADHD.

Not separating assessor from randomization is an additional limitation. Every measurement was assessed by the person who conducted the screening phase, so as not to be blinded from randomization. Although we tried to maintain an objective standpoint, we could not exclude observer bias, which all researchers brought to their work and which helped to determine their method of research and their observations. To minimize this bias, we involved objective ADHD measurement tools, like CNT40 and FAIR.

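### The claim of concealed allocation is not supported, because the principal investigator made the list and also controlled entry

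*Protocol article*

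**What the plan says.** In the Protocol article, under Randomization and treatment allocation, "The principal investigator generated the random allocation sequences without any notice to sub-investigators". The list is stratified by drug treatment at entry (envelopes 1-60 without, D1-D40 with) in blocks of 4. Assignments sit in opaque, consecutively numbered envelopes, and a child receives the next number once found eligible. The section then says: "The screener was unaware of the sequence of group allocation at the time of screening phase". From this it concludes that allocation was concealed during recruitment.

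Other sections assign these roles:

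- Participants: entry requires "having a diagnosis of ADHD (any subtype) according to Diagnostic and Statistical Manual of Mental Disorders (DSM-IV) criteria".
- Measures: the DSM-IV criteria "were used by the principal investigator to establish a diagnosis". Also: "Once randomised, participants were evaluated by the principal investigator during study visits at baseline and weeks 3 and 6".
- Primary outcome measures: "The principal investigator administered the K-ADHD-RS to the parent at each study visit". The same section says that national norms for this scale served to decide eligibility.
- Discussion: "Every measurement was assessed by the person who conducted the screening phase". The authors list as a limitation that assessor and randomisation were not kept apart. They discuss it as observer bias and offer CNT40 and FAIR as the remedy.

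**The concern.** Concealment means that whoever decides on entry cannot foresee the next assignment. Here the person who produced the list is also the person whose diagnosis admits a child. If that person can look up the next assignment, the decision to enrol, defer or decline can depend on it. The two groups may then differ from the start in ways that randomisation was meant to prevent.

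The safeguard matters more than usual in this trial. The trial is open, the control group waits, and the primary outcome is a parent-reported scale administered by an unblinded investigator. A reader who relies on the randomisation section would credit the trial with a protection that its other sections do not bear out. CNT40 and FAIR make measurement more objective, but they cannot undo selection at entry.

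**Working it through.** **1. Who does what, by section**

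| Role | Person | Section |
|---|---|---|
| Generates the sequence | Principal investigator | Randomization and treatment allocation |
| Makes the diagnosis required for entry | Principal investigator | Participants; Measures |
| Evaluates at baseline and follow-up | Principal investigator | Measures |
| Administers the K-ADHD-RS | Principal investigator | Primary outcome measures |
| Screens | Same person as the assessor | Discussion |
| Screener's knowledge of the sequence | None | Randomization and treatment allocation |

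**2. What follows**

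- By Measures and Primary outcome measures, the assessor is the principal investigator. By the Discussion, the assessor is the screener. So the screener is the principal investigator, who generated the list. The last row of the table cannot stand with the others.
- A shorter route does not need the Discussion. Envelope numbers follow eligibility, eligibility needs the DSM-IV diagnosis, and the list-maker gives that diagnosis. The list-maker therefore controls entry, whoever took the first telephone call.
- The K-ADHD-RS link is somewhat weaker. Measures speaks of a baseline evaluation once participants were randomised, while the Abstract places the first rating before randomisation. The diagnosis link does not depend on this.

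**3. Size**

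The article gives no figure for concealment. The only figure needed from it is the total of 80, which reproduces: 2 × (1.960 + 0.842)² × 9.9² / 7.04² = 31.04, so 32 per group; 32 / 0.80 = 40 per group, or 80 in all. The sample size is not at issue.

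A person with the list can know 100% of assignments, whatever the block size.

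**4. Secondary: fixed blocks of 4**

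Suppose someone without the list knows the block size and all earlier assignments in the stratum. Six arrangements of two A and two W are equally likely.

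- Certain in advance: the fourth place always, and the third when the first two agree (2 of 6 arrangements). That is 1 + 1/3 = 1.33 of 4, or 33.3%. Over 80 children in complete blocks, 80 × 0.333 is about 27.
- Best guess correct: 1/2 + 2/3 + 2/3 + 1 = 2.833 of 4, or 70.8%, against 50% without blocking.

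Now take equally likely blocks of 2, 4 and 6, with the size of the current block unknown to the guesser.

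- Best guess correct (always the under-represented arm): 1.5 + 2.833 + 4.1 = 8.433 per 12 assignments, or 70.3%.
- Certain in advance: only within blocks of 6. When one arm takes the first three places (2 of 20 arrangements), three places are certain. When the pattern is AAWA or its mirror (2 of 20), two are certain. That is 0.1 × 3 + 0.1 × 2 = 0.5 per 12 assignments, or about 4%.
- Largest imbalance within a stratum: half the largest block, so 3 instead of 2.

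Varied blocks therefore cut the certain share sharply and leave the best-guess rate almost unchanged.

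**The case against.** The strongest reply is that no section names the screener. The randomisation section sets the principal investigator apart from sub-investigators who were not told the sequence. Participants describes a first screen by telephone, and numbering is tied to the parent's call. A sub-investigator who took the calls would fit an unaware screener, and one loose use of a role name elsewhere would remove part of the conflict. This stands so far as it goes: a reader might infer that the principal investigator was certainly the screener, and the documents support that only by joining sections. It does not rescue concealment, because the diagnosis that admits a child is still made by the list-maker. Opaque envelopes hide the sequence from others, not from its author.

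The second reply is that the Discussion already discloses the problem. It does concede the overlap of roles. But it draws only the consequence for measurement and leaves the concealment claim uncorrected.

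The third reply is that blocks of 4 in two strata are ordinary practice, and that nothing shows that recruiting staff knew the block size. This stands, and the block-size point is secondary for that reason.

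Three stronger readings are not supported:

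- That selection took place. The text shows only that it was possible.
- That the type I error rises to some stated level. This would need the size of the shift caused by selection, for which the documents give no source.
- That steering milder children into group A would favour acupuncture. The primary outcome is change from baseline, and milder children have less room to improve, so the direction is doubtful. Selecting children expected to respond would clearly favour group A, and adjusting for baseline severity would not remove that.

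**Conclusion.** The point holds in this form: the article asserts concealed allocation, while its own account of roles gives the list and the entry decision to the same person. The claim is unsupported as written. The missing acknowledgement is narrow: selection bias is not named beside observer bias.

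The conclusion assumes that the role names mean what they say and that the principal investigator kept access to the list after generating it, since no handover to another custodian is described. Under these assumptions every assignment was open to the person controlling entry. The size and direction of any resulting bias cannot be estimated from the documents. The 33% for blocks of 4 holds only for someone who knows the block size and earlier assignments in the stratum, and the main conclusion does not rest on it.

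**What to change.** **Remaining allocations.** Recruitment and withdrawals describes recruitment as ongoing. Withdraw the unused envelopes. An existing colleague who neither screens, diagnoses nor rates should generate a new list for each stratum and hold it, and the principal investigator should keep no copy. Eligibility should be signed before the envelope is opened.

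**Children already randomised.** Reconcile Measures, Primary outcome measures, Randomization and treatment allocation, and the Discussion, so that it is clear who generated and held the list, who diagnosed, who screened and who rated. Withdraw the claim of concealment for these children and name selection bias as a limitation. If recruitment has ended, this is the part that remains, and it costs almost nothing.

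**Optional.** Vary the block sizes in the new list (for example 2, 4 and 6). This cuts the certain share but hardly changes the best-guess rate, so it is no substitute for separating the roles.

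**Cost.** A short amendment and about an hour of a colleague's time. The sample size is unchanged. Varied blocks up to 6 can leave an imbalance of up to 3 per stratum, against 2 with blocks of 4, and abandoning a part-used block of 4 can add up to 2.

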### Sample size justification

Sample size calculations are performed to determine the number of participants needed to detect effect sizes similar to those that have been reported in recent ADHD medication trials [56]. This study is powered to detect a 7.04 difference between the groups. A sample size of 32 per group is required to achieve 80% power with a 2-tailed significance level of .05, assuming an equivalent standard deviation of 9.9 in both groups. Estimating a 20% dropout during the study, a minimum of 80 total participants are needed to reach the target 32 participants per group [, μ_c _- μ_t_: Mean difference = 7.04, σ^2 ^= Assumed Common Variance of both treatment and control group (Standard Deviation = 9.9), n = 32]

### Recruitment and withdrawals

Recruitment for the study commenced in July 2010 and the first participant was enrolled in July 2010. Participant recruitment is ongoing. Each participant is qualified and enrolled into the study separately, and has their own start date. The study end-point goal is December 2011. Paid advertisements were placed in free-newspapers with metropolitan-wide circulations. Paid advertising bills were also inserted between the pages of the morning newspaper. Websites advertisements were placed on several blogs for free, including http://www.ebombit.com and happiend.tistory.com. Short, text-only advertisements were also placed on several ADHD parents' internet community sites for free. As part of the informed consent forms, the parents of the participants were advised that they were free to withdraw their child/children from the study at any stage without any consequences.

### Protocol

Group A (acupuncture group) continued with their existing program and the acupuncture protocol was added to their regimen. Group W (waitlist group) continued with their existing program and the waitlist protocol was added to their regimen. The participants in group A attended a clinical facility for the first 6 weeks and received 12 treatments (two times per week) for approximately 20 minutes. During this first 6-week period, group W consisted of children who continued with their existing ADHD treatment regimen as prescribed by their pediatrician, clinical psychologist and/or medical doctor. Then, the participants in group W were scheduled for another 12 treatments over the next 6 weeks (same as group A, two times per week).

### Acupuncture protocol

#### Definition of acupuncture

Acupuncture originated in ancient East Asia approximately 2,500 years ago and is a key component of traditional Korean medicine or traditional Chinese medicine. Acupuncture techniques involve insertion of needles and the stimulation of the needles may involve manual, electrical, heat, laser or other forms of stimulation [57].

#### Acupuncture protocol

For every treatment visit, participants are treated with 13 acupuncture points [Baihui (GV20)*1, Sishencong (EX-HN1)*4, Hegu (LI4)*2, Quchi (LI11)*2, Sanyinjiao (SP6)*2, Taichong (LR3)*2] (Table 1) [58]. Points are first sterilized with alcohol, and then thin, disposable acupunctures are inserted to a depth of approximately 0.3-0.5 B-cun (head: 0.3 B-cun; arms and legs: 0.5 B-cun) until a characteristic de qi is felt by the patient without manual stimulation. Acupunctures are maintained for 20 minutes in a supine position. Stainless steel acupunctures (0.20 mm in diameter and 30 mm long; DONGBANG Acupuncture; http://www.dbneedle.com; Seoul, Korea) are used. This treatment is conducted two times per week for 6 weeks. There are no co-interventions without a life-style education for their parents. An education for parents is conducted during visits in weeks 3 and 6.

**Table 1 T1:** Acupuncture points selected in this protocol

Acupuncture point	location
Baihui (GV20)	On the head, 5 B-cun superior to the anterior hairline, on the anterior median line. Note 1: GV20 is located in the depression 1 B-cun anterior to the midpoint of the line from the anterior hairline to the posterior hairline. Note 2: When the ears are folded, GV20 is located at the midpoint of the connecting line between the auricular apices.
Sishencong (EX-HN1)	EX-HN1 is located four points on the vertex of the head, 1 B-cun anterior, posterior and lateral to GV20.
Hegu (LI4)	On the dorsum of the hand, radial to the midpoint of the second metacarpal bone.
Quchi (LI11)	On the lateral aspect of the elbow, at the midpoint of the line connecting LU5 with the lateral epicondyle of the humerus. Note: When the elbow is fully flexed, LI11 is located in the depression on the lateral end of the cubital crease.
Sanyinjiao (SP6)	On the tibial aspect of the leg, posterior to the medial border of the tivia, 3 B-cun superior to the prominence of the medial malleolus. Note: 1 B-cun superior to KI8.
Taichong (LR3)	On the dorsum of the foot, between the first and second metatarsal bones, in the depression distal to the junction of the bases of the two bones, over the dorsalis pedis artery.

* B-cun: Proportional bone cun. This method divides the height of the human body into 75 equal units. Using joints on the surface of the body as the primary landmarks, the length and width of every body part is measured by such proportions.

